**DAY 7: 1st Vaccination Safety Follow-up (D7  $\pm$  1 day)**

- Collect diary card and review entries for completeness and accuracy
- Concomitant medication and adverse event review
- Standard haematology, clinical chemistry, coagulation and urinalysis assessments (as described in section 6.6.2)
- Vital signs after 5 minutes in a resting position (seated blood pressure, heart rate, respiratory rate and axillary body temperature).

**DAY 28: 2nd Vaccination (D28 + 7 days)**

**Prior to the vaccine administration:**

- Physical examination including weight;
- Vital signs after 5 minutes in a resting position (seated blood pressure, heart rate, respiratory rate and axillary body temperature)
- Concomitant medication and adverse event review
- Urine dipstick pregnancy test (for females of child-bearing potential only)
- CD4+ T cell counts
- HIV-1 plasma viraemia
- Anti-Tat antibodies (IgM, IgG, IgA)
- Immunological & Virological sample collection and storage.

Note: If the subject has a body temperature  $\geq 37.5$  °C or in the investigator's opinion, an acute illness, DO NOT VACCINATE; re-schedule the vaccination visit within the protocol specified window period i.e. Day 28 + 7 days.

**Vaccine administration:**

The next unused vial will be removed from the treatment kit previously allocated to the subject. The vaccine will be diluted and administered as described in section 5.1.

**Post-vaccination procedures:**

After administration of the investigational product, subjects will remain at the study centre for 2 hours for the following assessments, provided at 0.5 hours, 1 hour and 2 hours after vaccination, respectively:

- Symptom-directed physical examination.
- Vital signs after 5 minutes in a resting position (seated blood pressure, heart rate, respiratory rate and axillary body temperature).
- Assessment of adverse events.
- Distribute and review diary card and diary card instructions.

During this period the subject will not consume any food or beverages other than water.

Prior to discharge from the clinical facility, subjects will be counselled on ARV adherence, risk reduction and the prevention of pregnancy. The next visit will be scheduled for 7 days (Day 35  $\pm$  1 day) later.

**DAY 35: 2nd Vaccination Safety Follow-up (D35  $\pm$  1 day)**

- Collect diary card and review entries for completeness and accuracy
- Concomitant medication and adverse event review.
- Standard haematology, clinical chemistry, coagulation and urinalysis assessments (as described in section 6.6.2).
- Vital signs after 5 minutes in a resting position (seated blood pressure, heart rate, respiratory rate and axillary body temperature).

**DAY 56: 3rd Vaccination (Day 56 +7 days)**

**Prior to the vaccine administration:**

- Physical examination including weight
- Vital signs after 5 minutes in a resting position (seated blood pressure, heart rate, respiratory rate and axillary body temperature)
- Concomitant medication and adverse event review
- Urine dipstick pregnancy test (for females of child-bearing potential only)
- CD4+ T cell counts
- HIV-1 plasma viraemia
- Anti-Tat antibodies (IgM, IgG, IgA)
- Immunological & Virological sample collection and storage.

Note: If the subject has a body temperature  $\geq 37.5$  °C or in the investigator's opinion, an acute illness, DO NOT VACCINATE; re-schedule the vaccination visit within the specified window period i.e. Day 56 + 7 days.

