**Post-vaccination procedures:**

After administration of the investigational product, subjects will remain at the study centre for 2 hours for the following assessments provided at 0.5 hours, 1 hour and 2 hours after vaccination respectively:

- Symptom-directed physical examination.

- Vital signs after 5 minutes in a resting position (seated blood pressure, heart rate, respiratory rate and axillary body temperature).
- Assessment of adverse events.
- Distribute and review diary card and diary card instructions.

During this period the subject will not consume any food or beverages other than water.

Prior to discharge from the clinical facility, subjects will be counselled on ARV adherence, risk reduction and the prevention of pregnancy. The next visit will be scheduled for 7 days (Day 63  $\pm$  1 day) later.

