**DAY 63: 3rd Vaccination Safety Follow-up (D63  $\pm$  1 day)**

- Collect diary card and review entries for completeness and accuracy
- Concomitant medication and adverse event review
- Standard haematology, clinical chemistry, coagulation and urinalysis assessments (as described in section 6.6.2)
- Vital signs after 5 minutes in a resting position (seated blood pressure, heart rate, respiratory rate and axillary body temperature).

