### 8.2 Secondary Endpoint Variables and Measurements

In order to evaluate the safety of the Tat protein vaccination schedule in the study population, the following secondary endpoints will be considered and compared between active and placebo groups:

- Changes in physical examination findings from baseline;
- Changes in vital signs from baseline;
- Adverse events (including local and systemic reactions to the vaccination schedule occurring during the course of the study);
- Changes in standard laboratory safety parameters from baseline

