### **9.8 Subject Diary and Temperature Monitoring**

Subjects will receive, and be instructed in, the operation of a daily adverse event diary and a thermometer to be used during the 7-day post-vaccination diary period after vaccine administration. The daily adverse event diary is a source document and will record solicited adverse events, daily thermometer assessments of body temperature, and any other adverse events. At the safety visits scheduled 7 days after each vaccination the diary card will be collected and reviewed by the principal investigator (or designee) at which time any clinical details required for complete understanding of the information recorded will be obtained. Diaries not brought to the scheduled visit should be obtained before adverse event assessment can be performed. Lost diaries will be reconstructed as possible on a new diary booklet by the subject from memory at the closest clinic visit and labeled as a reconstructed diary. Adverse events obtained from the diary will be recorded and completely assessed on the Adverse Event CRF. Body temperatures below 38° C will not be considered fevers.

Any change to an AE recorded by the subject on the diary card (e.g., the severity level of an event is changed after interviewing the subject) based on the investigator's evaluation of the event must be explained by notation in source documentation.

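### Doses 2 and 3 may be given up to 7 days late, but their 7-day safety visits stay fixed at Day 35 ± 1 and Day 63 ± 1, so for a dose 3 to 7 days late no day satisfies both rules

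*Protocol*

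**What the plan says.** **When the doses may be given.** In section 6.7, a subject with fever or acute illness at the second vaccination is not vaccinated, and the site is to "re-schedule the vaccination visit within the protocol specified window period i.e. Day 28 + 7 days". The third vaccination has the same rule: "re-schedule the vaccination visit within the specified window period i.e. Day 56 + 7 days". Both windows run late only. Section 9.6 applies the same 7-day allowance to a missed vaccination visit.

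**When the safety visit happens.** After dose 2, section 6.7 says "The next visit will be scheduled for 7 days (Day 35", with ± 1 day attached to that day number. The visit's own heading, "Vaccination Safety Follow-up (D35", carries the same ± 1 day. Dose 3 is handled identically: "The next visit will be scheduled for 7 days (Day 63" and "Vaccination Safety Follow-up (D63", each again with ± 1 day on the day number. Appendix II lists the visits under Days 35 and 63.

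**What the visit is for.** Section 9.8 ties the visit to the dose: "At the safety visits scheduled 7 days after each vaccination the diary card will be collected". Section 6.7 adds haematology, clinical chemistry, coagulation and urinalysis at the same visit. Section 8.2 makes local and systemic reactions secondary endpoints, along with "Changes in standard laboratory safety parameters from baseline".

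**The concern.** The two definitions of the safety visit agree only if the dose is on time or nearly so. No text in section 6.7 or Appendix II moves the visit when the dose moves, so for a late dose the site has to choose which rule to break.

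- **If it keeps the fixed day,** the 7-day diary is collected before it is complete and the laboratory panel is drawn early, at worst no more than a day after the dose. Appendix II schedules no safety laboratory tests on Day 28 or Day 56, so the early panel is not replaced.
- **If it counts 7 days from the dose,** the visit falls outside its stated window and is a deviation on paper.

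Subjects may be handled differently, and those affected include people whose dose was postponed because they were febrile or ill.

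**Working it through.** **Inputs (all protocol).** Dose 2 on Day 28 + k and dose 3 on Day 56 + k, with k = 0 to 7 days late (section 6.7). Fixed visit windows of Days 34–36 and Days 62–64 (section 6.7). Dose-relative target of 7 days after the dose (sections 6.7 and 9.8), read generously as 6 to 8 days.

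**The plan's own figures.** With on-time dosing, 28 + 7 = 35 and 56 + 7 = 63, as printed.

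**Late dosing.** Counted from the dose, the fixed window for dose 2 runs from 34 − (28 + k) = 6 − k to 36 − (28 + k) = 8 − k days. It overlaps the 6-to-8-day target only if 8 − k ≥ 6, that is k ≤ 2. For dose 3, 62 − (56 + k) and 64 − (56 + k) give the same expressions.

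| Days late (k) | Dose 2 day | 7 ± 1 days after dose | Days also in 34–36 | Fixed window, days after dose |
|---|---|---|---|---|
| 0 | 28 | 34–36 | 34, 35, 36 | 6 to 8 |
| 1 | 29 | 35–37 | 35, 36 | 5 to 7 |
| 2 | 30 | 36–38 | 36 | 4 to 6 |
| 3 | 31 | 37–39 | none | 3 to 5 |
| 4 | 32 | 38–40 | none | 2 to 4 |
| 5 | 33 | 39–41 | none | 1 to 3 |
| 6 | 34 | 40–42 | none | 0 to 2 |
| 7 | 35 | 41–43 | none | −1 to 1 |

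For dose 3, add 28 to every day number; the pattern is unchanged. No compliant day exists for k = 3 to 7, which is 5 of 8 permitted dose days. If exactly 7 days is required, the condition is 28 + k + 7 ≤ 36, so k ≤ 1, and 6 of 8 dose days have none.

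**Gap to the next safety panel if the fixed day is kept, at k = 7.**

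- Dose 2 on Day 35: the next panel is at Days 62–64, so 62 − 35 = 27 to 64 − 35 = 29 days after the dose, and normally after dose 3.
- Dose 3 on Day 63: the next panel is the Day 84 ± 7 visit, Days 77–91, so 77 − 63 = 14 to 91 − 63 = 28 days after the dose.

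**The case against.** The best reply is that the protocol already means the visit to follow the dose. Section 9.8 says so, and the visit exists to collect a 7-day diary that is handed out only after the injection. After dose 1, section 6.7 attaches the ± 1 day to the 7-day interval. Appendix II shows no windows for any visit and lists the doses themselves at bare Days 28 and 56, so its columns are evidently nominal. A sensible site would count from the dose, incur a window deviation, and lose no data.

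Even if the fixed day were kept, adverse events are collected throughout the 48 weeks and reviewed at later visits, the rule is the same in both blinded arms, section 12.7 plans only summaries of laboratory change, and the antibody endpoint is untouched.

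Much of this stands. The dose-relative reading is the more sensible one, Appendix II is weak evidence on its own, and the early-panel and long-gap consequences arise only if the fixed day is kept. But the contrast with dose 1 also cuts the other way: after doses 2 and 3 the tolerance sits on the day number, both in the scheduling sentence and in the visit heading. Nothing says that section 9.8 overrides those headings. A site that does the sensible thing is still outside a written ± 1 day window that monitors are asked to check (section 11.2).

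**Conclusion.** The concern holds. This is a contradiction between stated rules, not a detail left for later. For doses 3 to 7 days late, no visit day is both 7 ± 1 days after the dose and within the printed window, for dose 2 and dose 3 alike.

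The 5-of-8 figure counts permitted dose days. It is not a proportion of subjects, because the documents give no frequency of late doses. The practical impact is modest: it touches the timing of one diary collection and one laboratory panel per late dose, both feeding secondary safety endpoints. It does not affect the primary antibody comparison or the sample size. The first safety visit (Day 7 ± 1) is unaffected, since Day 0 is the dose day.

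**What to change.** In section 6.7 (the scheduling sentences after doses 2 and 3, and the two safety follow-up headings), define each visit as 7 ± 1 days after the actual date of that vaccination, and keep Day 35 and Day 63 as nominal labels. Add a footnote to Appendix II saying the same. Leave the dose windows as they are.

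Every permitted dose day then has a 3-day visit window. The latest visits become Day 35 + 8 = 43, before dose 3 opens on Day 56, and Day 63 + 8 = 71, before the earliest Day 84 visit on 84 − 7 = Day 77. No other visit is displaced.

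The cost is two headings, two sentences and one footnote. Dosing, number of visits, blood volume, endpoints and sample size do not change.

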**Vaccine administration:**

The next unused vial will be removed from the treatment kit previously allocated to the subject. The vaccine will be diluted and administered as described in section 5.1.

**Post-vaccination procedures:**

After administration of the investigational product, subjects will remain at the study centre for 2 hours for the following assessments provided at 0.5 hours, 1 hour and 2 hours after vaccination respectively:

- Symptom-directed physical examination.

- Vital signs after 5 minutes in a resting position (seated blood pressure, heart rate, respiratory rate and axillary body temperature).
- Assessment of adverse events.
- Distribute and review diary card and diary card instructions.

During this period the subject will not consume any food or beverages other than water.

Prior to discharge from the clinical facility, subjects will be counselled on ARV adherence, risk reduction and the prevention of pregnancy. The next visit will be scheduled for 7 days (Day 63  $\pm$  1 day) later.

**DAY 63: 3rd Vaccination Safety Follow-up (D63  $\pm$  1 day)**

- Collect diary card and review entries for completeness and accuracy
- Concomitant medication and adverse event review
- Standard haematology, clinical chemistry, coagulation and urinalysis assessments (as described in section 6.6.2)
- Vital signs after 5 minutes in a resting position (seated blood pressure, heart rate, respiratory rate and axillary body temperature).

**DAY 84: First follow-up visit (Day 84  $\pm$  7 days)**

The following procedures and assessments will be performed on all subjects:

- Physical examination including weight
- Vital signs after 5 minutes in a resting position (seated blood pressure, heart rate, respiratory rate and axillary body temperature)
- Concomitant medication and adverse event review
- Standard haematology, clinical chemistry, coagulation and urinalysis assessments (as described in section 6.6.2)
- CD4+ T cell counts
- HIV-1 plasma viraemia
- Anti-Tat antibodies (IgM, IgG, IgA)
- Immunological & Virological sample collection and storage
- Counselling on ARV adherence, risk reduction and the prevention of pregnancy.

**DAY 112: Second follow-up visit (Day 112  $\pm$  7 days)**

The following procedures and assessments will be performed on all subjects:

- Physical examination including weight
- Vital signs after 5 minutes in a resting position (seated blood pressure, heart rate, respiratory rate and axillary body temperature)
- Concomitant medication and adverse event review
- Standard haematology, clinical chemistry, coagulation and urinalysis assessments (as described in section 6.6.2)
- CD4+ T cell counts
- HIV-1 plasma viraemia
- Anti-Tat antibodies (IgM, IgG, IgA)
- Immunological & Virological sample collection and storage
- Counselling on ARV adherence, risk reduction and the prevention of pregnancy.

**DAY 140: Third follow-up visit (Day 140  $\pm$  7 days)**

The following procedures and assessments will be performed on all subjects:

- Physical examination including weight

- Vital signs after 5 minutes in a resting position (seated blood pressure, heart rate, respiratory rate and axillary body temperature)
- Concomitant medication and adverse event review
- Standard haematology, clinical chemistry, coagulation and urinalysis assessments (as described in section 6.6.2)
- CD4+ T cell counts
- HIV-1 plasma viraemia
- Anti-Tat antibodies (IgM, IgG, IgA)
- Cervical swab and Pap smear for detection of HPV infection (Female participants only)
- Immunological & Virological sample collection and storage
- Counselling on ARV adherence, risk reduction and the prevention of pregnancy.

**DAY 168: Fourth follow-up visit (Day 168 ± 7 days)**

The following procedures and assessments will be performed on all subjects:

- Physical examination including weight
- Vital signs after 5 minutes in a resting position (seated blood pressure, heart rate, respiratory rate and axillary body temperature)
- Concomitant medication and adverse event review
- Standard haematology, clinical chemistry, coagulation and urinalysis assessments (as described in section 6.6.2)
- CD4+ T cell counts
- HIV-1 plasma viraemia
- Anti-Tat antibodies (IgM, IgG, IgA)
- Immunological & Virological sample collection and storage
- Counselling on ARV adherence, risk reduction and the prevention of pregnancy.

**DAY 336: Study termination (Day 336 ± 7 days)**

The following procedures and assessments will be performed on all subjects:

- Physical examination including weight
- Vital signs after 5 minutes in a resting position (seated blood pressure, heart rate, respiratory rate and axillary body temperature)
- Concomitant medication and adverse event review
- Standard haematology, clinical chemistry, coagulation and urinalysis assessments (as described in section 6.6.2)
- Urine dipstick pregnancy test (for females of child-bearing potential only)
- CD4+ T cell counts
- HIV-1 plasma viraemia
- Anti-Tat antibodies (IgM, IgG, IgA)
- Cervical swab and Pap smear for detection of HPV infection (Female participants only)
- Immunological & Virological sample collection and storage
- Counselling on ARV adherence, risk reduction and the prevention of pregnancy.

**DAY 343: Dissemination of results (Day 343 ± 7 days)**

Within 7 days of the study termination visit, a site staff member will telephonically contact the subject to inform them of the results of the following tests done at the study termination visit:

- Standard haematology, clinical chemistry, coagulation and urinalysis assessments
- Urine dipstick pregnancy test (for females of child-bearing potential only)

- CD4+ T cell counts
- HIV-1 plasma viraemia

Results of the Pap smear will be telephonically communicated to the subject as soon as they become available.

In both cases, if results are abnormal and require that the subject be referred to a health facility, the subject will be requested to visit the site for the collection of a referral letter.

## **6.8 Compliance**

IP will be administered by designated clinical study personnel at the clinical site only. Treatment compliance will be verified by the CRA during monitoring visits. Drug accountability records will be completed according to the SOPs of the CRO and will be cross-checked with the investigational product at the site during monitoring visits.

*The subject will be reminded of the importance of attending the visits according to the planned timelines as strictly as possible.*

## **7 PREVIOUS AND CONCOMITANT MEDICATION**

*A reasonable effort will be made to determine all relevant pharmacological and non-pharmacological treatments received by the subject during the 4 month period prior to the screening visit.*

*Subjects are permitted to receive standard therapy for any medical condition, including treatment for any viral or bacterial or other infections that develop during the study.*

*Chronic stable therapy (e.g., antihypertensive therapy) will be permitted throughout the study provided that subjects remain on a constant dose from 30 days prior to the first vaccination administration until the end of the study duration.*

*All previous and concomitant treatments will be recorded in the CRF, including the name of the treatment (if pharmacological, only generic names are required unless it is a combination product where the trade name should be documented), indication, route, total daily dose and start/stop dates.*

### **7.1 Antiretroviral Therapy**

*Subject should receive standard antiretroviral therapy in accordance with their clinical condition and local, current guidelines.*

*As far as possible, a complete antiretroviral treatment history, starting from the first antiretroviral therapy taken by the subject, must be recorded in the CRF.*

### **7.2 Prohibited Medication/Therapy**

*The following medications will not be allowed for the duration of the study period:*

- antipsychotic medications (throughout the study period);
- immunomodulators (for 30 days prior to screening and throughout the study period);
- immunosuppressants (for 30 days prior to screening and throughout the study period);
- anticoagulants (for 30 days prior to screening and throughout the study period);

- *blood products or immunoglobulins (for 1 year prior to screening and throughout the study period);*
- *live attenuated vaccines (for 60 days prior to the first administration of the investigational product and throughout the study period); and/or*
- *CCR5 inhibitors and/or integrase inhibitors and/or fusion inhibitors (for 6 months prior to screening and throughout the study period)*

A subject who takes any of the above-mentioned treatments during the 8 week active treatment period will be withdrawn from further vaccination, but will continue to be followed for safety for the entire study period. Their data will however not be used in the immunogenicity analysis.

## 8 ENDPOINTS

### 8.1 Primary Endpoint Variable and Measurements

In order to evaluate the immunogenicity of Tat protein in the study population, the following primary endpoint will be considered:

- Induction of specific anti-Tat humoral immune response in terms of IgM, IgG or IgA anti-Tat antibodies.

The induction, magnitude and persistence of the humoral response to the administered vaccination schedule will be compared between the active and placebo groups.

The induction of the anti-Tat specific **humoral immune response** will be evaluated in the active as compared to the placebo group as follows:

1. Percentage of “responders”, defined as those subjects that develop an immune response greater than the following levels:
  - *Anti-Tat IgM titers  $\geq 25$*
  - *Anti-Tat IgG titers  $\geq 100$*
  - *Anti-Tat IgA titers  $\geq 25$*
2. Geometric mean antibody titers (GMT) induced by vaccination.

### 8.2 Secondary Endpoint Variables and Measurements

In order to evaluate the safety of the Tat protein vaccination schedule in the study population, the following secondary endpoints will be considered and compared between active and placebo groups:

- Changes in physical examination findings from baseline;
- Changes in vital signs from baseline;
- Adverse events (including local and systemic reactions to the vaccination schedule occurring during the course of the study);
- Changes in standard laboratory safety parameters from baseline

